# Repetitive Transcranial Magnetic Stimulation (rTMS) for the cognitive rehabilitation of traumatic brain injury (TBI) victims: study protocol for a randomized controlled trial

**DOI:** 10.1186/s13063-015-0944-2

**Published:** 2015-10-05

**Keywords:** Brain Injury, Cognition, Cognitive, Diffuse Axonal Injury, Non-invasive brain stimulation, Psychology, Repetitive transcranial magnetic stimulation (TMS, rTMS)

## Abstract

**Background:**

Repetitive Transcranial Magnetic Stimulation (rTMS) has been proposed as a new tool in neurological rehabilitation of victims of traumatic brain injury (TBI). However, its usefulness to treat this condition has never been tested rigorously. The primary goal is to conduct a study protocol to determine whether rTMS used to cognitive rehabilitation of victims of TBI with diffuse axonal injury (DAI) is a safe instrument and if it enhances cognitive function recovery.

**Methods:**

Double-blind randomized controlled trial of patients with diffuse axonal injury. Thirty-six patients will be randomized to either an active coil group or sham group in a 1:1 ratio. rTMS protocol: 10 sessions of high-frequency rTMS (10 Hz) over the left dorsolateral prefrontal cortex (DLPFC). Cortical Excitability measures will be obtained. Neuropsychological evaluations will be performed 1 week before, 1 week and 3 months after rTMS. There are 2 study hypotheses: (1) rTMS over the left DLPFC in patients with DAI will improve cognitive function and (2) whether rTMS is safe in TBI patients.

**Discussion:**

This study evaluates the immediate and delayed effects of rTMS over the DLPFC on the cognitive domain of patients with DAI following TBI. rTMS has shown good results in treating major depression and may be promising for patients with TBI. As such, the results of this study can greatly modify the cognitive rehabilitation strategies.

**Trial registration:**

This trial was registered in clinicaltrials.gov (NCT02167971) on 17 June 2014.

## Background

### Epidemiology

Traumatic brain injury (TBI) remains as a global health problem that generates a major socioeconomic impact worldwide. Estimates indicate that TBI accounts for 9 % of global mortality and, more significantly, each death is related to dozens of hospitalizations, hundreds of medical appointments at the emergency departments and thousands of ambulatory consultations [1, 2]. This significant global adverse impact of TBI includes a major impact on Brazil, since cognitive sequelae among the survivors increase each year. According to Maset et al. [3], 360 cases/100,000 inhabitants per year is the reported incidence of TBI in Brazil.

### Pathophysiology

Traumatic axonal injury, also referred as diffuse axonal injury (DAI), is responsible for almost one third of deaths due to TBI and is the leading cause of disability among survivors, including not only motor deficits but also cognitive impairment and mood disorders [4, 5].

Regarding the pathogenesis of DAI, the basic structural damage is axotomy. Two basic mechanisms are suggested: primary axotomy and secondary axotomy. Primary axotomy occurs immediately after the tissue injury, allowing calcium influx and activation of the inflammatory cascade. Then follows secondary axotomy which happens hours after the trauma and can last for many years [6–9].

### Neuropsychological aspects

TBI is associated with a variety of disturbances in cognition and transient neurological deficits [10]. DAI is a common mechanism of injury in brain trauma associated with cognitive impairment, emotional and behavior disorders [11]. Cognitive impairment can be persistent, especially in moderate and severe injuries and deficits include: decreased executive functions and attentional process, judgment, verbal fluency, information processing and memory [12–14]. DAI patients can show diffuse cognitive impairments that may change over time due to secondary injury sequelae and Wallerian degeneration [15]. Imaging studies identified that the brain regions typically involved in DAI are: frontal regions, cingulate, thalamus and corpus callosum, resulting in decreasing of global intelligence [16], losses in executive functions, episodic memory and attentional process [17, 18].

### Rationale for a neuromodulation study in TBI

The number and type of neuropsychiatric conditions being treated by repetitive Transcranial Magnetic Stimulation (rTMS) is ever increasing [19, 20].

Several studies have demonstrated improvement in some cognitive aspects after rTMS [20–24]. Notably, rTMS may have cognitive enhancing properties and is under investigation for a variety of drug-resistant disorders [20]. A substantial and growing interest for the rTMS application of TMS in TBI patients has been seen, with encouraging results for the treatment of specific symptoms [25–28].

The rational use of rTMS for DAI patients is based on the perspective that induction changes in cortical excitability may lead to reorganization of a network responsible for an impaired cognitive function. This function may be restored or compensated by mechanisms involving structural and functional changes in brain circuits [25–27].

The intended use of rTMS is to enhance positive neuroplastic changes that could represent real improvement in the cognitive domain (such as working memory), quality of life and in mood disorder. Thus, neuropsychological assessments on rTMS studies can help measuring early and late cognitive and behavioral changes on TBI patients after the intervention.

### Study purpose and objectives

The clinical goal is to assess safety and determine whether high-frequency rTMS of the left dorsolateral prefrontal cortex (DLPFC) is effective for the cognitive rehabilitation of DAI patients after TBI.

### Primary outcome measures

The primary hypothesis is that the active coil group will show improvement between baseline and last early assessment of > 1 standard deviation on the Trail Making Test part B (TMTB), in comparison to the sham-treated patients The TMTB is known for its accurate assessment of executive function in mild and moderate TBI.

### Secondary outcome measures

Evaluate the complications and technical difficulties of the proposed protocolAssess early and late performance after rTMS on the neuropsychological battery, which will include: memory and executive functions, attention, learning and processing speed; intensity of depressive symptoms, and intensity of anxious symptomsCompare cortical excitability with single-pulse and paired-pulse TMS between the active and sham coil groups.

## Methods

### Protocol proposal

#### General aspects

By the time this protocol was written in 2014, there were over 10,000 TMS manuscripts cataloged on PubMed [29], with at least 2,000 focusing on rTMS. However, to the best of our knowledge, there is no randomized controlled trial with rTMS in patients with TBI. Therefore, we propose the application of a promising instrument, which has already proved to be effective in many psychiatric and neurological conditions, in a population of chronic subjects, many of them disabled, with very few treatment options in terms of cognitive functional recovery.

#### Study design

This is a prospective, single-center, randomized, parallel-group controlled trial that will be held at the Hospital das Clínicas, University of São Paulo, São Paulo, Brazil. Study Recruitment started in January 2014 and the estimated study completion date for the primary outcome is September 2015.

This trial will follow the main CONSORT (Consolidated Standards of Reporting Trials) guidelines as well as its extension to non-pharmacological interventions. This protocol will also adhere to SPIRIT (Standard Protocol Items: Recommendations for Interventional Trials) guidelines.

#### Inclusion criteria

Patients older than 18 and younger than 60 years will be included. Only patients with clinical and radiological diagnosis of traumatic DAI after 1 year of TBI will be included. All the patients have to be able to answer the neuropsychological battery.

#### Exclusion criteria

Patients will be excluded if they have any of the following:Prior history of epilepsyExtensive cranial vault defectsDrug addictionPregnancy or are lactating mothersHave a cardiac pacemaker or a cochlear implantHave an implanted device (e.g. deep brain stimulator, ventriculoperitoneal shunt) or metal in the brain (e.g. aneurysm clip)Known psychotic disorderTBI within last 12 months

### Study intervention

#### Standard care

All patients will keep their clinical follow-up at the Neurotrauma Outpatient Clinics independently of the study and group assignment by other physicians not involved in this study.

### rTMS protocol

#### Magnetic stimulator

The rTMS will be performed with a commercially available MagPROX100 (Magventure Tonika Elektronic, Farum, Denmark) equipped with a focal figure-of-8-shaped coil (active coil model: MCF-B65 and sham coil model: MCF-P-B65) with continuous water cooling system to prevent overheating during stimulations. The sham coil has the same size and shape of the active coil. It also emits a noise very similar to the active one, but it does not create any significant magnetic field.

#### Target

rTMS will be applied with a figure-of-8-shaped coil centered over the left DLPFC, based on the F3 position of the International 10–20 system, using the modification described by Beam et al. [30]. We will perform 10 daily sessions in both groups (5 consecutive weekdays, 2 days-off during weekends and another 5 consecutive weekdays).

#### rTMS sessions

Every session will be held at the Service of Interdisciplinary Neuromodulation, *Hospital das Clínicas* – University of São Paulo, with the same machine and at the same daytime. Each session will consist of 50 trains of 40 pulses on each train separated by 25-second pauses applied at 10 Hz frequency, at an intensity of 110 % of the patient’s resting motor threshold (RMT) intensity.

### Resting motor threshold

RMT intensity was defined as the lowest stimulation intensity that, in 10 trials, induced at least 5 motor evoked potentials of at least 50-μV peak-to-peak amplitude assessed on the first dorsal interosseus muscle in the resting state.

#### Cortical excitability

The measurements will be performed before rTMS sessions, immediately after the last rTMS session (10th session) and 90 days after the completion of stimulations and will include: RMT measured in percentage of the maximum machine output, short-interval cortical inhibition (SICI) with interstimulus interval (ISI) of 2 and 4 mS, and intracortical facilitation (ICF) with ISI of 10 and 15 mS, both of them measured by paired-pulse TMS.

Figure 1 shows the timeline of the study protocol.

**Fig. 1 Fig1:**
[figure not shown]
Timeline: this figure summarizes the study protocol. There will be 13encounters (D1–D13): 2 encounters before the stimulations and 2 after (follow-up). CE: cortical excitability; D1–D13: day (encounter) 1 to 13; IC: informed consent; NA: neuropsychological assessment; PainQ: pain questionnaires (*Douleur Neuropathique* 4 (DN4), McGill, and visual analogic scale (VAS)); rTMS: Repetitive Transcranial Magnetic Stimulation

### Subjects and recruitment

This study will include 36 patients from 18 to 60 years old, both genders, who have participated in previous observational prospective study of neuropsychological aspects and quality of life on victims of TBI. We will recruit patients who sustained DAI after TBI, based on clinical history and magnetic resonance imaging (MRI) findings confirming DAI. All eligible recruited patients will be randomly divided into two groups. During the screening period, all patients will receive a unique identification number, which will be used along the study to keep the staff blinded.

Throughout the study, regular documented clinical follow-up, evaluation instrument scales and possible telephone contact will be used to measure and maintain patient compliance.

#### Baseline measures

The following characteristics will be assessed at baseline: age, gender, handedness, time from TBI, level of schooling, mechanism of trauma, current use of medications, Glasgow coma scale at hospital admission, and prevalence of pain.

#### Evaluation of the prevalence of pain

The patients will be evaluated during the study about the presence of pain. If positive, this will be assessed with the visual analogic scale (VAS) score, DN4 (*Douleur Neuropathique* 4), and The McGill Pain Questionnaire. This questioning will be done before and after the rTMS sessions.

#### Randomization and blinding

Randomization will be done via a computer-produced randomized controlled table. Thirty-six patients will be randomized in 1:1 ratio into 2 groups: active coil group and sham coil group. This is a double-blind study, which the neuropsychologists and the patients (as well as their relatives) will be blinded for the group assignment. Only two of the authors involved directly with the rTMS application will assign participants to interventions.

#### Blinding and allocation concealment committee

This study involves the participation of a medical committee, not directly related to the patient group assignment, who can remove the blinding in caseany clinical condition arises that would be relevant to group assignment, adverse event, or patient dropout.

## Informed consent

Only patients who give informed written consent will be included in this study.

### Safety considerations and adverse events

This protocol is in accordance to the most recent guidelines about rTMS reported by Rossi et al. [31].

As per each meeting, patients will be questioned about adverse events and the information will be recorded and published. If a major adverse event occurs (e.g. seizure), the subject will receive medical assistance and further examination and investigation will be provided as needed. Family members will receive a feedback on the status of their relative who is enrolled in the study, and a contact number of the investigators and TMS clinic will be provided for further questions.

### Neuropsychological assessment

The neuropsychological evaluation will be performed in 3 phases, as follows:Evaluation 1: up to 3 months prior to rTMS sessions. The subjects will be submitted to the battery described below.Evaluation 2: up to 1 week after the completion of the rTMS sessions. The subjects will be submitted to the same battery as in Evaluation 1. This assessment aims to verify the rTMS’s early effects.Evaluation 3: 90 days after the conclusion of the rTMS sessions. This assessment will evaluate the delayed effects of the rTMS sessions.

Figure 2 demonstrates the study protocol flow and highlights the three time points when the neuropsychological assessments will be held.

**Fig. 2 Fig2:**
[figure not shown]
Study flow diagram: this study will recruit 36 patients from Hospital das Clínicas, University of São Paulo, Brazil. After baseline data collection, participants will be randomized to active coil group or sham coil group in a 1:1 ratio. Baseline assessment include standard history and clinical assessment, neurocognitive evaluation, prevalence of pain symptoms (assessed with the VAS, DN4, and The McGill Pain Questionnaire), MRI scan, and cortical excitability assessment with TMS. After the end of the intervention (rTMS), participants will undergo two revaluations (early and late data collection). DN4,*Douleur Neuropathique* 4, MRI, magnetic resonance imaging, TMS, Transcranial Magnetic Stimulation, rTMS, repetitive TMS, VAS, visual analogic scale

### Instruments

The following instruments will be applied during the three aforementioned evaluations: Beck Depression Inventory – BDI-II [32, 33]; State-Trait Anxiety Inventory (STAI) [34]; Focused and alternating attention: Trail Making Test parts A and B (TMTA and TMTB) [35]; Selective attention and inhibition: Stroop Test – Victoria version [36]; Verbal fluency [35, 36]; Five Points Test [37]; Symbol Digit Test (processing speed) [38]; Verbal learning and episodic long-term memory: Hopkins Verbal Learning Test – HVLT [39]; Brief Visuospatial Memory Test – BVMT [40]; Working memory (subscale of Wechsler Memory Scale – WAIS) [41]; Motor dexterity – Grooved Pegboard Test [42].

### Ethics committee and regulatory approval

The trial will be conducted in accordance with the ethical principles outlined in the Declaration of Helsinki, 1996. This research was approved by the Hospital das Clínicas, University of São Paulo Ethical Institutional Review Board (IRB #193.985/13). The present study has been approved by COSEPE (Sectorial Commission of Ethics in Research – Division of Psychology, Hospital das Clínicas – University of São Paulo) #18/2010 and CAPPESQ (Ethics Committee for review of research projects, Hospital das Clínicas – University of São Paulo) process #0097/11.

### Data analysis

The SPSS 19.0 software package for Windows (SPSS Inc., Chicago, IL, USA) will be used for all statistical analyses. The *T* test will be used for comparison between means and Chi-squared test for proportions. Non-parametric analysis will include Wilcoxon and Mann–Whitney tests. A significance level of *p* < 0.05 will be chosen for all tests. A fully specified statistical analysis plan will be written before unmasking the study in order to guarantee replicability and to avoid outcome selective reporting. All the analysis will be based on “as randomized” patients.

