### Sample size

We have considered a difference of 1 standard deviation in TMTB, an 80 % power, and an alpha of 5 %, a minimum of 15 participants are needed for each group. We will add three patients per group to compensate for possible loss of follow-up. Thereafter, 18 patients will be allocated to each group.

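### Only t-tests and rank tests are named for a change-from-baseline outcome; ANCOVA on the baseline TMTB already collected would usually be more precise, at almost no cost

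*Protocol article*

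**What the plan says.** The Data analysis section lists the methods in general terms. The T "test will be used for comparison between means and Chi-squared test for proportions", and "Non-parametric analysis will include Wilcoxon and Mann–Whitney tests". The 5% level applies to every test. No test is tied to the primary outcome, and no model with a baseline covariate appears. A full statistical analysis plan is promised before unmasking, and patients are to be analysed in the group to which they were randomised.

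Under Primary outcome measures, the outcome is improvement in TMTB from baseline to the early assessment, active against sham. TMTB belongs to the battery given at all three evaluations (Instruments). For Evaluation 2, "The subjects will be submitted to the same battery as in Evaluation 1". Baseline TMTB is therefore available for every patient assessed as planned.

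On size: "We have considered a difference of 1 standard deviation in TMTB", with "an 80 % power, and an alpha of 5" per cent, so that "a minimum of 15 participants are needed for each group". Three more per group are added for loss, giving 18. The section does not say whether the standard deviation is that of the score or of the change, or whether the test is one- or two-sided.

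**The concern.** With 15 to 18 patients per arm, the arms can differ noticeably at baseline by chance. A follow-up-only comparison ignores such a difference. A change score over-corrects for it whenever r is below 1, with equal variances. ANCOVA estimates how much correction the data support, and so usually has a smaller standard error.

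At stake is precision in a small trial whose power at 15 completers per arm is slightly below target under a two-sided t-test. The covariate is already being collected, so using it needs no extra patients or visits.

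**Working it through.** **Inputs.** From Sample size: a difference of 1 SD, 80% power, alpha 5%, 15 per group, 18 with the allowance. Assumed, because the documents do not give them: a two-sided test, equal variances at both times, and r, which is varied.

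**The plan's own figure.** Normal formula: n = 2(1.960 + 0.842)² / 1² = 15.70, so 16 per arm. Power at 15 is 78.2%. The stated 15 is thus reproduced to within one patient. An exact two-sided t-test (noncentral t, 28 df, noncentrality √(15/2) = 2.74) has 75.3% at 15 and needs 17 per arm. Power is 80.7% at 17 and 83.0% at 18. A one-sided t-test would need 14. For Mann–Whitney, assuming normal data and relative efficiency 0.955, power is about 73% at 15 and 81% at 18.

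**Variance.** With score variance σ²:
- change score: 2σ²(1−r)
- ANCOVA residual: σ²(1−r²)
- ratio: (1−r²) / [2(1−r)] = (1+r)/2, which is 0.75 at r=0.5 and 0.85 at r=0.7.

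**Power at 15 per arm if 1 SD is the SD of the score.** Standardised effects are 1/√(2(1−r)) for change and 1/√(1−r²) for ANCOVA (27 df). A follow-up-only t-test has 75.3% throughout.

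| r | effect, change | effect, ANCOVA | power, change | power, ANCOVA |
|---|---|---|---|---|
| 0.3 | 0.845 | 1.048 | 60.8% | 79.0% |
| 0.4 | 0.913 | 1.091 | 67.5% | 82.1% |
| 0.5 | 1.000 | 1.155 | 75.3% | 86.2% |
| 0.7 | 1.291 | 1.400 | 92.7% | 95.9% |

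ANCOVA reaches 80% for r of about 0.34 or more.

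**Power at 15 per arm if 1 SD is the SD of the change.** The change-score t-test has 75.3% at every r. The ANCOVA effect is 1/√((1+r)/2).

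| r | effect, ANCOVA | power, ANCOVA |
|---|---|---|
| 0.2 | 1.291 | 92.6% |
| 0.5 | 1.155 | 86.2% |
| 0.7 | 1.085 | 81.7% |
| 0.8 | 1.054 | 79.5% |
| 0.9 | 1.026 | 77.3% |

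ANCOVA reaches 80% for r of about 0.775 or less.

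**A small refinement.** These ANCOVA figures charge the lost degree of freedom but not the chance difference between the arms' baseline means. That difference inflates the variance on average by 1 + 1/(2n−4) = 1 + 1/26 = 1.038 at n=15. Including it lowers the tabulated powers by about 0.6 to 1.6 points and moves the two thresholds to about 0.38 and 0.71. In the worst case on the score reading, r=0, ANCOVA then has 73.6% against 75.3% for the follow-up-only test.

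**Chance imbalance.** The standard error of the baseline difference is √(2/n): 0.37 SD at 15 per arm and 0.33 SD at 18. A difference above 0.5 SD arises in about 17% and 13% of such trials, taking simple randomisation. Given a difference b, the expected shift is −(1−r)b for the change score and +rb for the follow-up score. With b=0.5 SD and r=0.5, each is 0.25 SD in size.

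**What bears on r.** The abstract puts the pre-treatment evaluation 1 week before rTMS; Neuropsychological assessment allows up to 3 months. A longer gap would tend to lower r, and on the score reading a low r is where the change score does worst.

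**The case against.** The strongest reply is that the article lists generic tests and defers the full specification to a later plan, so the choice of model is not yet fixed. That is right as far as it goes. A reader might infer that the protocol commits the primary outcome to an unadjusted test; it does not, and an adjusted analysis is not ruled out. What stands is narrower: every between-group method it names for a continuous outcome lacks baseline adjustment, and a better one is available from data already planned.

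Three other strong readings also fail.

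- *The analysis is biased or ignores baseline.* The outcome is a change, so baseline already enters. Under randomisation the change-score t-test is unbiased with the correct type I error, and its standard error allows for chance imbalance. The issue is efficiency.
- *The trial is short of power and ANCOVA would restore it.* The gap is 2 to 5 points at 15 completers per arm under a two-sided test, and absent at 17 or 18. On the score reading, the change-score test already has 92.7% at r=0.7. Whether ANCOVA reaches 80% at 15 depends on an r that is not given and on which SD is meant.
- *The named tests conflict with analysis as randomised because missed visits drop out.* The sentence beginning "All the analysis will be based on" most naturally means analysis by assigned group. ANCOVA at Evaluation 2 loses the same patients as a t-test there, so missing visits are no argument for it.

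**Conclusion.** The point holds as a recommendation on efficiency. The named tests are valid, but ANCOVA on baseline TMTB would usually do better. The gain at 15 per arm ranges from large (61% to 79% power at r=0.3, score reading) to small (75% to 77% at r=0.9, change reading), and the possible loss is at most about 2 points. ANCOVA would probably, but not certainly, close the modest gap at 15 completers per arm. These figures rest on two-sided testing, normal data, equal variances and an assumed r. It should be acted on, but it does not invalidate the design.

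**What to change.** In the analysis plan, before unmasking, name one primary analysis: ANCOVA of TMTB at Evaluation 2 on group, with TMTB at Evaluation 1 as covariate, two-sided 5%, patients analysed in their assigned group. State in advance whether completion times will be transformed if skewed. Keep the t-test and Mann–Whitney test as sensitivity analyses. State also whether the 1 SD in the sample size is of the score or of the change.

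Optionally, fit one baseline-adjusted repeated-measures mixed model to Evaluations 2 and 3, so that a patient who misses one of the two still contributes.

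The cost is one degree of freedom, the small variance allowance shown above, and some wording. No new patients, visits or measurements are needed.

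### The only tests named for the TMTB change are unadjusted, though baseline TMTB is collected on every patient and only 15 to 18 per arm are planned

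*Protocol article*

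**What the plan says.** Under Primary outcome measures, the hypothesis concerns "improvement between baseline and last early assessment of > 1 standard deviation on the Trail Making Test part B (TMTB"), in comparison with sham. This is a change from baseline compared between two arms.

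Under Data analysis, the t "test will be used for comparison between means", and "Non-parametric analysis will include Wilcoxon and Mann–Whitney tests". No covariate and no transformation is named. The section then defers detail: "A fully specified statistical analysis plan will be written before unmasking the study".

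Under Sample size: "We have considered a difference of 1 standard deviation in TMTB", and "a minimum of 15 participants are needed for each group". Three more per arm are added for loss to follow-up, giving 18. The text does not say whether the SD is that of the score or of its change.

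Under Instruments, TMTB belongs to the battery given at all three evaluations, so a baseline value exists for each patient. The scoring unit is not given.

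**The concern.** Subtracting baseline is not the same as adjusting for it. When the correlation between baseline and follow-up is below 1, the change score over-corrects: it carries the noise of the baseline measurement at full weight. A model with baseline as covariate uses the weight that the data support and has a smaller residual variance. A t test or a Mann-Whitney test on the change forgoes that gain.

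The loss matters here because the sample is small and the design has almost no reserve. At 15 evaluable per arm the planned t test is already a little under its 80% target. If TMTB is a right-skewed time, a few slow patients can also dominate the SD of the change, and the loss is larger.

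**Working it through.** **1. The plan's own figure.** Inputs from Sample size: difference 1 SD, power 80%, alpha 5% (two-sided assumed).
- Normal approximation: n = 2 × (1.96 + 0.84)² = 15.7, so 16 per arm. The stated 15 is close.
- Allowance for loss: 15 / (1 − 3/18) = 18.
- Exact two-sided t test: power 0.753 at 15 per arm, 0.807 at 17 and 0.830 at 18.

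**2. Baseline adjustment with normal scores.** Let σ be the SD at both visits and r the baseline to follow-up correlation (assumed 0.5 to 0.8).
- Variance of the change: 2σ²(1 − r).
- Residual variance given baseline: σ²(1 − r²).
- Ratio: (1 + r)/2, which is 0.75, 0.85 and 0.90 at r = 0.5, 0.7 and 0.8.

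For an effect of 1 SD of the change, the noncentrality is √(n/2) = 2.739 for the t test at n = 15. For the adjusted model it is 2.739 × √(2/(1 + r)) × √(26/27), where the last factor allows for chance baseline imbalance. The adjusted model has 27 degrees of freedom.

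| r | noncentrality, adjusted | power, change t test | power, adjusted |
|---|---|---|---|
| 0.5 | 3.103 | 0.753 | 0.849 |
| 0.7 | 2.915 | 0.753 | 0.802 |
| 0.8 | 2.833 | 0.753 | 0.780 |

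The gain is about 3 to 10 points. Simulation with normal times (mean 150 s, SD 30 or 45 s, both assumed) agrees: 0.74-0.76 for the change t test and 0.77-0.85 for the adjusted model. The variance ratio does not depend on which SD the plan means by 1 SD.

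**3. Baseline adjustment with skewed times.** Assumed: lognormal times, log-SD 0.2 to 0.5, r = 0.5 to 0.8, effect 1 SD of the log change, 15 per arm, 20,000 simulated trials per cell. Ranges run over r.

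| log-SD | raw-change t | raw-change Mann-Whitney | raw ANCOVA | log ANCOVA |
|---|---|---|---|---|
| 0.2 | 0.70-0.71 | 0.66-0.68 | 0.77-0.84 | 0.78-0.85 |
| 0.3 | 0.65-0.67 | 0.63-0.65 | 0.75-0.83 | 0.78-0.85 |
| 0.5 | 0.55-0.58 | 0.57-0.60 | 0.71-0.79 | 0.78-0.85 |

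Baseline adjustment in raw units gains about 6 to 24 points over the raw-change t test. Mann-Whitney on the change does not recover the loss. Type I error stayed at 0.043-0.052 for all these tests.

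**4. How much is the log?** At log-SD 0.5 and r = 0.7: raw-change t 0.57, raw ANCOVA 0.73, t test on log change 0.75, log ANCOVA 0.80. Adding the log to an adjusted model gains 7 points there, but only 1 point at log-SD 0.2 (0.79 to 0.80).

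**5. The log when there is no skew.** In the normal-times simulation of step 2, log ANCOVA is about 1.5 to 5 points below raw ANCOVA. In a separate normal-times run with coefficient of variation 0.33 and r = 0.7 it fell to 0.66, below the 0.75 of the raw-change t test.

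**The case against.** The strongest reply is that the article condenses a plan that is to be fully specified before unmasking, and that covariates and transformations are what such a plan settles. That stands as far as missing detail goes: the absence of a named covariate is not an error in itself. It does not remove the point, because the tests the article does name are unadjusted and a better method is available from data already collected.

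A reader might go further and infer that the trial will analyse raw seconds, that the times are strongly skewed, and that a log model is therefore required. The documents do not support this. They state no scoring unit, SD or distribution, and a t test on log or normed scores would also fit the text. Nor can a long slow tail be inferred from an absence of severity limits, since the Inclusion criteria require patients to be able to answer the battery.

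The skewed-times figures also fix the effect at 1 SD of the log change, not at the plan's 1 SD in TMTB. At log-SD 0.5 and r = 0.7 that is only 0.77 SD of the raw change, so part of the shortfall of the raw t test comes from how the effect is defined. This is a fair limit on step 3. It does not touch step 2, where the effect is 1 SD of the raw change.

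**Conclusion.** The point holds for baseline adjustment. The named tests discard usable precision in a trial with 15 to 18 per arm. In every shape tried, the adjusted model in raw units beat the t test on change: by about 3 to 10 points with normal scores, and by about 6 to 24 points with lognormal times at log-SD 0.2 to 0.5. The log scale is a secondary choice: it helps if times are skewed and costs power if they are not.

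All power figures rest on assumed correlations of 0.5 to 0.8 and assumed distributions. The direction for normal scores follows from the ratio (1 + r)/2, which is below 1 for any r below 1. Where r is very close to 1, the gain becomes negligible. The named tests keep their type I error, so this is an improvement in efficiency and not a matter of validity.

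**What to change.** In Data analysis, and in the statistical analysis plan before unmasking, make the primary analysis a linear model of TMTB at Evaluation 2 on arm and baseline TMTB (Evaluation 1). Report the adjusted difference with a 95% confidence interval. Keep the t test and Mann-Whitney on the change as sensitivity analyses.

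State the TMTB scoring unit. If it is completion time in seconds, fix before unmasking whether outcome and baseline are both log-transformed, with the effect then reported as a ratio of times.

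The change is one of wording. It needs no new data or patients, and baseline adjustment uses one degree of freedom. The log scale, if chosen, makes the effect a ratio rather than a difference and carries the power cost in step 5 if the times turn out near normal.
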